## Abstract

**Background:**

Neurofeedback (NF) enables the self-regulation of brain activity through real-time feedback extracted from brain measures. Recently, the combination of several neuroimaging methods to characterize brain activity has led to growing interest in NF. The integration of various portable recording techniques, such as electroencephalography (EEG) and functional near-infrared spectroscopy (fNIRS), respectively based on electrical and hemodynamic activity, could enhance the characterization of brain responses and subsequently improve NF performance. Such multimodal NF used with motor imagery (MI) could benefit post-stroke motor rehabilitation to stimulate neuroplasticity of the lesioned motor areas. Nevertheless, their concomitant use in NF to identify brain activity features during upper-limb MI-based NF has not been studied to our knowledge. The objective of this paper is to present our fully operational experimental platform and the study protocol we propose to assess the benefits of combining EEG and fNIRS for NF in the context of MI.

**Methods:**

We developed a custom experimental platform, including a cap integrating EEG and fNIRS sensors, along with software for real-time signal processing, NF score calculation and visual feedback presentation. To evaluate the effect of EEG-fNIRS NF in the context of MI, thirty right-handed participants will undergo three randomized NF conditions: EEG-only, fNIRS-only and EEG-fNIRS based NF. EEG electrodes and fNIRS channels will be positioned above the sensorimotor cortices. Participants will be presented with a visual representation of a ball along a one-dimensional gauge moving upwards according to their brain activity level as they perform a MI task of their left-hand. An NF score will be computed from the right primary motor cortex activity along the three different experimental conditions (EEG-only, fNIRS-only, EEG-fNIRS). The association between the NF score, the neuroimaging modality and the motor imagery strategy will then be analyzed.

**Discussion:**

The designed experimental platform allows combined EEG-fNIRS NF. The presented study protocol will be the first investigation of the effects of multimodal neurofeedback using EEG and fNIRS during upper-limb MI tasks. We hypothesize that presenting the participants with a visual NF representing a score based on both EEG and fNIRS signals will result in more specific task-related brain activity in the sensorimotor cortices. With potentially increased neuroplasticity, such a system could find applications in clinical contexts, particularly in motor rehabilitation, for example in post-stroke units.

## 1. Background

Neurofeedback (NF) is a neuroscientific method that aims to enhance brain efficiency. NF enables the self-regulation of brain activity through real-time feedback (e.g., visual, auditory or other sensory representations) extracted from brain measures [1]. Neurofeedback can lead to measurable and lasting changes in brain activity, reflecting functional plasticity [2]. This process is often conceptualized in terms of operant conditioning, where successful modulation of neural activity is positively reinforced [3]. This process may lead to improvements in behavior, physical health, cognition and emotional functioning [3–6]. NF has been explored for a variety of clinical [7–10] and non-clinical applications [3–6,11,12]. However, its effective integration into clinical practice is hindered by ongoing debates over its efficacy, likely due to issues such as poor study design, a lack of standardized guidelines and limited understanding of its underlying mechanisms [12,13]. One reason for the contested efficacy of current approaches might be the inherent limitations of single imaging modalities [14,15].

As NF focuses on the activity of the central nervous system, a key challenge in its application is to determine which neuroimaging method and strategy to use (e.g., NF metaphor, mental task, design). Neurofeedback studies often report that approximately 30% of participants face difficulties in self-regulating their brain activity [16]. These challenges may arise from suboptimal feature selection, design flaws in feedbacks, tasks and instructions [17,18], individual anatomical and physiological differences that reduce responsiveness to specific modalities [19]. Each neuroimaging modality captures specific biophysical aspects of brain activity but is subject to different technical and physiological limitations [14]. The field of NF originates from electroencephalography (EEG), which measures rapid changes in electrical potentials across the scalp and is valued for its portability, non-invasiveness and high temporal resolution [20]. On the other hand, over recent decades, researchers have explored neurovascular coupling through functional magnetic resonance imaging (fMRI; [21]) and more recently, through functional near-infrared spectroscopy (fNIRS) which tracks changes in oxygenated (HbO_2_) and deoxygenated (HbR) hemoglobin in cortical regions [22,23]. Both fMRI and fNIRS methods offer higher spatial resolution but lower temporal resolution than EEG. Compared to fMRI, fNIRS is a cost-effective, portable and adaptable tool for hemodynamic-based real-time applications in an ecological context. Nevertheless, fNIRS also presents a lower spatial resolution and limited depth but offers a higher temporal resolution. While unimodal techniques provide valuable insights, their limitations can be mitigated by combining complementary modalities which is really promising in the field of brain computer interface (BCI) to decode brain activity [24,25].

Recently, there has been growing interest in integrating multiple brain activity measurement technologies. The integration of these technologies offers a novel approach that leverages the strengths of each while addressing their individual limitations [26]. This concept involves combining various recording techniques to enhance the performance of NF, with studies demonstrating the advantages of multimodal acquisition systems compared to unimodal ones [27,28]. The most prevalent multimodal system involves the concurrent use of fMRI and EEG. This combination capitalizes on EEG high temporal resolution and fMRI superior spatial resolution, providing a complementary approach to neurofeedback [27,29–32]. It has also been tested in post-stroke clinical contexts [33,34]. However, this approach has significant drawbacks related to fMRI inherent limitations, such as high operating and acquisition costs, the contraindications related to the use of fMRI and the need for almost total immobilization of the patient in a lying position [35].

Another multimodal system under development is fNIRS-EEG, a mobile setup that facilitates use in ecological contexts, such as clinical environments [36]. EEG and fNIRS share mutual information by picturing the cortical brain activity, yet also exhibit important distinct features with for example the recording of electrical activity and hemodynamic variations. For example, the study by Fazli et al. [15] demonstrated that EEG and fNIRS complement each other in terms of information content with information gained from various sources, making them a viable multimodal imaging technique suitable for BCI. Regarding the association of fNIRS and EEG in NF, Zich et al [37] proposed a multimodal neuroimaging framework that focuses on EEG-derived event-related desynchronization (ERD, i.e., decrease in neural oscillatory power activities within EEG signals during movement execution, [38]) and fNIRS-based measures of HbO_2_ and HbR. They identified significant modulation correlations between ERD and hemodynamic measures, despite the absence of significant amplitude correlations. However, in their study, the authors used the fNIRS signal for offline analysis presenting EEG unimodal NF in real-time only [37]. A review exploring fNIRS-EEG-based BCIs suggests that combining peak and mean fNIRS signals with the highest band powers of EEG signals is promising for multimodal BCIs to improve the system accuracy [39]. In the context of eating disorders, another study demonstrated that EEG- and fNIRS-based NF produced similar outcomes, although the authors did not integrate both signals into a unified NF approach [40]. Finally, simultaneous measurement of fNIRS and EEG is easy to combine and use in neuroimaging studies for other applications (for reviews see [40,41]). Therefore, it could be highly relevant to apply this combination to NF and develop methodologies for real-time analysis of both signals.

Although multimodal EEG-fNIRS is considered to combine the advantages of EEG and fNIRS in a way that compensates for the limitations of each modality, its potential to record cerebral activity features has not been comprehensively investigated [26]. In motor rehabilitation, motor imagery (MI) – the mental representation of an action without its actual execution [42] – is commonly incorporated into NF protocols to target brain motor areas, making it a suitable task for anticipating later clinical application [9]. To our knowledge, no study has explored the effect of multimodal EEG-fNIRS-based NF in the context of MI. Thus, the aim of this paper is to evaluate the efficiency of EEG-fNIRS-based NF for MI in comparison to unimodal EEG-based and fNIRS-based NF. To reach this objective, we developed and implemented an experimental platform for multimodal EEG-fNIRS NF in the context of upper limb (UL) MI. Implementing such multimodal systems presents significant challenges, including the need for seamless coordination and synchronization of two inherently distinct systems, while maintaining real-time performance and ensuring that they do not interfere with each other. We then designed a randomized controlled study with healthy volunteers to assess the potential of multimodal EEG-fNIRS NF. We hypothesize that presenting participants with visual NF based on a combined score from both EEG and fNIRS signals will result in higher sensorimotor brain activity reflected in both EEG and fNIRS signals. As exploratory outcomes, we will investigate the participants’ feeling of NF control, the relationship between the motor imagery vividness (i.e., ability to build image and kinesthetic sensation of a movement) and the NF score. We will start by presenting the designed and already operational experimental platform and will then present the study protocol proposed to evaluate the effects of EEG-fNIRS based NF.

## 2. Methods

### 2.1. Experimental platform

In order to evaluate the effect of multimodal EEG-fNIRS NF for MI of the left upper limb, we designed and implemented an experimental platform. The experimental platform was implemented for block design protocols and requires a step of calibration for parameterization of the score calculation. This platform contains a homemade cap-layout combining EEG and fNIRS sensors specifically designed for our NF target and an application software to receive and process signals in real-time, calculate an NF score and present the user with a visual NF. The source code is accessible from a git repository (https://gitlab.inria.fr/empenn-public/neurofeedback/fNIRS-EEG-NFB) and archived on Software Heritage (swh:1:dir:6433906c87451098cd3e324215715ba552396399).

#### 2.1.1. *Cap-layout.*

To simultaneously record EEG and fNIRS data, we designed a cap-layout using a 32-channel EEG system (ActiCHamp, Brain Products GmbH, Gilching, Germany) and a continuous wave NIRS system with 16 detectors, 16 LED sources (λ1|2 = 760|850 nm) and 8 short channels (NIRScout XP, NIRx, Berlin, Germany). All sensors are installed on an EasyCap (Easy-cap, CNX-128 Cap, Brain Products GmbH, Gilching, Germany). Based on the 10−10 international system, we positioned 19 of the 32 EEG channels above the sensorimotor cortices (FC5, FC3, FC1, FC2, FC4, FC6, C5, C3, C1, C2, C4, C6, CZ, CP5, CP3, CP1, CP2, CP4, CP6). Additionally, three electrodes are placed above the occipital cortices (OZ, O1, O2), four above the frontal areas (Fp1, Fp2, F3, F4, Fz), two above the temporal regions (T7, T8) and three above the parietal region (Pz, P3, P4). For the fNIRS channels, we positioned the optodes over both sensorimotor cortices, with 22 long channels (source-detector distance = 3 cm) and 4 short channels (source-detector distance = 0.8 cm) over the left sensorimotor area (SM), and 24 long and 4 short channels over the right SM. The difference in the number of channels is due to the use of detector 16 (D16) to connect the 8 short channels. Fig 1 shows the complete layout of all EEG and fNIRS sensors on the cap.

**Fig 1 pone.0331177.g001:**
[figure not shown]
Set-up designed for our NF-platform. Brain cap layout on the 10−10 international system. Nz (Nasion), Iz (Inion), LPA (left pre-auricular), RPA (right pre-auricular). EEG channels are in green, fNIRS detectors in blue, fNIRS sources in red and fNIRS channels in purple. The short channels are connected to detector 16 and their sources are shown in red surrounded by a black circle.

#### 2.1.2. *NF features real-time preprocessing.*

**EEG.** In our platform, the EEG feature for NF is defined as the ERD in the alpha band (8–13 Hz) of the EEG data. The raw EEG signal undergoes several preprocessing steps. First, Fz is set as the reference electrode. Next, only the electrodes that superimpose the brain area of interest are kept (in our subsequent study, we will consider C4, FC2, FC6, CP2 and CP6). Then, a spatial filter (Laplacian, 43) is applied to enhance the signal from the electrode representing the NF target, here C4 (i.e., left hand representation in the primary motor cortex, [43,44]). The filter coefficients are: C4 (4), FC2 (−1), FC6 (−1), CP2 (−1), and CP6 (−1). To calculate a weighted difference between the signal at the central channel and the signals from its immediate surrounding neighbors, a positive coefficient (+4) is assigned to the central channel (C4), and negative coefficients (−1) are assigned to its surrounding neighboring channels (FC2, FC6, CP2, CP6). A band-pass filter (order 4, cutoff frequencies 8–13 Hz) is then applied to the resulting signal in order to keep only the alpha-band that is used to calculate the NF score.

**fNIRS.** The fNIRS feature is based on the oxyhemoglobin change in concentration (ΔHbO_2_) computed from the two channels located above the target EEG channel (i.e., D1-S1; D2-S2 channels in the subsequent protocol study, see **Fig 1**). First, the raw intensity data are converted in real-time to optical density using the last 120 s of the signal [45]. Next, to remove extracortical components from the signal, a correction is performed using the short-channel signals by doing a systemic correction regression based on the nearest short channel [46–48]. We choose to apply the short-channel correction on the optical density value as in previous fNIRS-BCI studies [49]. Then, the corrected optical density signal is converted to variations in HbO2 and HbR concentrations using the modified Beer-Lambert law ([50]; ppf = 6.0). A band-pass filter (order 4, 0.01–0.09 Hz) is finally applied to remove potential confounding signals such as Mayer waves, heartbeat and breathing [49,51,52].

#### 2.1.3. *Neurofeedback score.*

**EEG-NF score.** A time-based epoching is applied to the EEG preprocessed signal to generate 1 s epochs occurring every 0.25 s. Then, the power of the EEG signal is computed. An EEG-NF score is calculated every 0.25 s based on 1.5 s periods (i.e., averaged over 3 epochs) using a 5 s rest periods (i.e., average of 17 epochs, see Fig 2). In order to prevent from temporal drift, the EEG-NF score is computed considering the last 5* seconds of the previous rest period as the baseline. The ERD ratio is then calculated:

**Fig 2 pone.0331177.g002:**
[figure not shown]
Epoching of the EEG and fNIRS signals. 1-A represents the epochs averaged for the rest period and 1-B for the task for the EEG signal. 2-A represents the epochs averaged for the rest period and 2-B for the NF task for the fNIRS signal.

$Ratio\;ERD=\frac{\left(pTask\;-pRest\right)}{pRest}*100$, where *pRest* represents the power averaged from the epochs from the last 5 s of the preceding rest period and *pTask* represents the power averaged from the last 1.5 s that capture the near-instantaneous power during the NF task [53]. A new ERD ratio is calculated every time a new epoch is received (i.e., every 0.25 s according to the time based epoching). During the calibration session, the 30th percentile of the ERD ratios is extracted from all the calibration blocks and set as the target level to reach 100% during the NF session. This choice was made based on previous NF protocols, in order to individually set the difficulty of the NF task (i.e., maximal value of the gauge). We chose to focus solely on the expected movement-related desynchronization, which is indicated by a negative ERD during the task [54]. This value is stored and used to compute the EEG-NF score: $NF_{EEG}=\;\frac{Ratio\;ERD\;(NF\;task)}{Ratio\;ERD\;(calibration)}*100$.

**fNIRS**-**NF score.** A time-based epoching is applied to generate epochs of 0.96 s every 0.48 s for the fNIRS (see Fig 3). The duration of the epochs and moving window of the fNIRS is based on the sampling frequency (i.e., 6.25 Hz), ensuring a constant and integer number of fNIRS samples across all epochs. A fNIRS NF score is calculated every 0.48 s based on 1.92 s periods (i.e., averaged of 3 epochs) using a 4.8 s rest periods (i.e., average of 9 epochs, see Fig 2). In order to prevent from temporal drift, the fNIRS-NF score is computed considering the last 4.8* seconds of the previous rest period as the baseline. The **diff*Δ*HbO**_*2*_ is then calculated as followed:

**Fig 3 pone.0331177.g003:**
[figure not shown]
Implementation of EEG and fNIRS from acquisition and real-time preprocessing of EEG and fNIRS signals to the calculation of the NF score. 1. Acquisition is done through the OpenViBE acquisition server for the EEG, and for the fNIRS the raw signal is recorded via the NIRStar software and transferred to the openViBE acquisition software via LSL communication. 2. Real-time preprocessing steps are conducted in the OpenViBE designer software.

**diff*Δ*HBO**_*2*_* = ΔHBO*_*2(Task)*_
**-* Δ*HBO**_*2(Rest*)_*,* where *ΔHBO*_*2(Rest)*_ represents the average of the epochs from the last 4.8 s of the preceding rest period and *ΔHbO*_*2(Task)*_ represents the average over the last 1.92 s reflecting the near-instantaneous relative variation in oxyhemoglobin concentration during the NF [49]. A new ΔHbO_2_ value will be calculated every 0.48 s. To follow the EEG targets, during the calibration session, the 30th percentile of the positive ΔHbO_2_ values as the target level to reach 100% during the NF session. This value will be stored and used to compute the fNIRS NF score:

$$\;NF_{fNIRS}\;=\;\frac{diff\Delta HBO_{2}\;(NF\;task)}{diff\Delta HBO_{2}\;(calibration)}*100.$$

We focus specifically on the expected response during movement, an increase in the relative ΔHBO_2_ concentration during the task is expected, which is reflected by a positive ΔHbO_2_ [55].

**EEG-fNIRS-NF score.** The EEG-fNIRS combined score is based on the average of the *NF*_*EEG*_ and *NF*_*fNIRS*_ scores. It is refreshed every time a new EEG or fNIRS score is calculated:

$$NF_{EEG\text{-}fNIRS}\;=\;\frac{{NF}_{EEG}+{NF}_{fNIRS}}{2}.$$

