**Neurofeedback score metaphor.** The implementation of the score metaphor is presented on Fig 4. We chose a visual feedback adapted from the work of Perronnet et al. (2020) [28]. The NF paradigm includes the use of a visual metaphor consisting of a vertical gauge with a yellow ball moving up and down in 1D. The ball position represents the EEG scores, fNIRS scores or the average of both EEG and fNIRS scores. The background of the 1D gauge is divided into four regions to provide the subject with reference points. The NF score calculation is carried out using a dedicated Python code (Python 3.12). Visual instructions and feedback are presented to the user using the PsychoPy toolbox (Peirce et al., 2019, version 2023.2.3 [60]). The ball position ranges from 0% to 100%. If the NF score exceeds 100%, it is capped at 100%, and if it is negative, it is set to 0%. Both the *NF*_*EEG*_ and *NF*_*fNIRS*_ score is transmitted to the Python Psychopy script through LSL and the ball position is updated accordingly. Every time a new score arrives, the ball position is updated.

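### As written, the fNIRS 100% target does not match the EEG target it is meant to follow: the same 30th percentile is demanding on the ERD scale and lenient on the HbO2 scale

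*Protocol article*

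**What the plan says.** All of this is in the protocol article.

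- **EEG target** (section 2.1.3, EEG-NF score): "the 30th percentile of the ERD ratios is extracted from all the calibration blocks and set as the target level to reach 100"%. The percentile is there "in order to individually set the difficulty of the NF task (i.e., maximal value of the gauge"). Success is a desynchronization, "which is indicated by a negative ERD during the task". The text adds "We chose to focus solely on the expected movement-related desynchronization", but does not say whether the percentile is taken over all ratios or only the negative ones.
- **fNIRS target** (section 2.1.3, fNIRS-NF score): "To follow the EEG targets, during the calibration session, the 30th percentile of the positive" HbO2 values becomes the 100% level. Success is an increase: a higher "concentration during the task is expected, which is reflected by a positive" change.
- **Scores**: each modality's score is its current value divided by its calibration target, times 100. "The EEG-fNIRS combined score is based on the average of the" two scores, with equal weights.
- **Display** (section 2.1.4, score metaphor): "If the NF score exceeds 100%, it is capped at 100%, and if it is negative, it is set to 0"%.
- **Use** (section 2.2.5): the primary outcome is the difference in brain activity between the three conditions. NF scores check that participants succeeded in each condition. They are listed with the brain-activity data for the ANOVA or Friedman comparison, and they enter the correlations with feeling of control. Feeling of control is itself compared across conditions.

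**The concern.** The percentile is the device that sets difficulty, and the fNIRS rule is introduced as following the EEG one. On a scale where lower is better, a 30th percentile is a level that few calibration values reach. On a scale where higher is better, it is a level that most reach. The stated rule therefore works against its stated purpose.

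If the rule ran as written, the conditions would differ in gauge difficulty as well as in modality. The fNIRS ball would sit at its ceiling more often, and gains above the ceiling would not be visible. The low fNIRS denominator would also enlarge the fNIRS part of the combined score. Between-condition differences in NF score or in feeling of control could then reflect the height of the bar rather than the signal behind it.

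**Working it through.** The article gives no attainment rate, so there is no figure to reproduce. The check uses the definition of a percentile. I read the fNIRS calibration values as task-minus-rest differences, because that is the denominator in the score formula.

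**Inputs.** From the article: 30th percentile in both modalities; success is low for EEG and high for fNIRS; only positive values enter the fNIRS percentile; ball limited to 0–100. Not in the article, so assumed: p, the share of calibration HbO2 values that are positive (range 0.3 to 1.0).

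**Step 1, values in the expected direction only.**
EEG: P(value ≤ 30th percentile) = 0.30.
fNIRS: P(value ≥ 30th percentile) = 1 − 0.30 = 0.70.

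**Step 2, literal text (EEG on all ratios, fNIRS on positive values).** EEG attainment is 0.30 of all windows. fNIRS attainment is 0.70 × p of all windows:

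| p | 0.3 | 0.5 | 0.6 | 0.7 | 0.8 | 0.9 | 1.0 |
|---|---|---|---|---|---|---|---|
| fNIRS | 21% | 35% | 42% | 49% | 56% | 63% | 70% |
| EEG | 30% | 30% | 30% | 30% | 30% | 30% | 30% |

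The two are equal at p = 0.30/0.70 = 0.43.

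**Step 3, effect on the gauge (literal text).** Assume the same normal distribution for both modalities: SD 1, mean shifted in the expected direction, NF response equal to calibration, score clipped to 0–100. Simulation with 2,000,000 values per case gives:

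| Mean shift (SD) | p | EEG target (SD) | fNIRS target (SD) | Mean gauge, EEG | Mean gauge, fNIRS |
|---|---|---|---|---|---|
| 0 | 0.50 | 0.53 | 0.39 | 40 | 42 |
| 0.5 | 0.69 | 1.03 | 0.54 | 50 | 59 |
| 1 | 0.84 | 1.53 | 0.78 | 59 | 73 |
| 2 | 0.98 | 2.52 | 1.52 | 72 | 87 |

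**Step 4, weight in the combined score.** Points gained per SD of response are inversely proportional to the target. Before any cap, one SD of fNIRS response counts 1.53/0.78 = 1.96 times one SD of EEG response at a shift of 1 SD, and 0.53/0.39 = 1.36 times at no shift.

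**Step 5, the mirrored rule.** The 70th percentile of all HbO2 values is reached by 30% of all windows, which equals the EEG rule on all ratios. The 70th percentile of positive values is reached by 0.30p of all windows (15% at p = 0.5, 24% at p = 0.8). This equals an EEG rule restricted to negative ratios when the share of values in the expected direction is the same, but is harder than an EEG rule on all ratios. The value set must therefore agree between modalities.

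**The case against.** Five points can fairly be made on the other side.

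1. **It may be a wording fault.** The intent to match EEG is stated, the fNIRS sentence lacks a main verb, and the code in the public repository is not visible here. This stands as a limit: a reader might infer that participants received an easier fNIRS gauge, and the article alone cannot show that. It does not rescue the stated rule, which needs correcting either way.
2. **A flat contrast of 70% against 30% mixes denominators** if the EEG percentile uses all ratios. This stands. The contrast is then 0.70p against 0.30, small at p = 0.5 and reversed below 0.43. A low p is possible for some participants: section 1 (Background) cites about 30% with difficulty self-regulating, and section 3 (Discussion) notes the delayed haemodynamic response. A p below 0.43 would, however, go against the increase that section 2.1.3 expects.
3. **The primary outcome is not computed from the targets.** This stands. A reader might infer that the primary comparison is directly biased, but it rests on offline EEG and fNIRS measures (section 2.2.4). The targets can act on it only through the feedback seen, and the documents do not allow the size or direction of that effect to be derived.
4. **Equal attainment is not equal difficulty**, since the modalities also differ in latency and update rate. True, but that is no reason to add a further difference that the text means to avoid.
5. **Changing the rule during acquisition has a cost.** This stands, and it shapes the fix.

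**Conclusion.** The point holds for the rule as written. The fNIRS target contradicts its stated aim of following the EEG target: among values in the expected direction, 70% reach it against 30% for EEG. Over all windows, with EEG on all ratios, fNIRS attainment is 35% to 70% for p from 0.5 to 1.0, against 30%. The fNIRS gauge is easier whenever the expected response occurs, and the gap widens as p rises. With identical normal signals and a 1 SD response, the mean gauge is 73 against 59. The equal-weight combined score then leans towards fNIRS.

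The direct consequence is that NF scores, and plausibly feeling of control, are not comparable across conditions at equal difficulty. The size rests on p, which the article does not give, on which ratios enter the EEG percentile, and, for the gauge averages, on the normal model. What feedback was actually delivered remains unknown until the code is checked.

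**What to change.** 1. **Correct the fNIRS rule in section 2.1.3** to the mirrored percentile and name the value set for each modality. If EEG uses all ratios, take the 70th percentile of all task-minus-rest HbO2 values. If EEG uses negative ratios only, take the 70th percentile of the positive values.
2. **State what the code ran**, with the software version. If it already mirrors the percentile, the correction is to the text only.
3. **If the 30th percentile ran on both**, keep the delivered rule the same for all participants unless acquisition has not materially progressed. Section 2.2 dates acquisition from 1 December 2024 to 30 June 2025, and a late switch would leave two versions of the feedback among thirty people.
4. **In that case, also re-score and report.** Recompute the fNIRS and combined scores offline from the stored calibration data with the mirrored target. Report the share of time at 100% by condition. Do not read between-condition differences in NF score or feeling of control as modality effects at equal difficulty.

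The cost is some re-scoring work and a disclosure that the delivered fNIRS gauge was easier. Re-scoring repairs the scores but cannot undo the feedback that participants saw. If all values are used, the target has the expected sign only when more than 30% of values lie in the expected direction, so a fallback for the remaining participants should be stated for both modalities.
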